### Mechanics of vertebroplasty

The mechanics of vertebroplasty underpin the treatment’s application and patient selection, and these principles need be clarified as they affect study design. We hypothesize that vertebroplasty is only effective when applied in the acute fracture setting in patients with severe pain. It can then potentially provide internal fixation and ameliorate the acute pain generated by fracture fragment motion. To achieve adequate internal fixation in a collapsing bone, we believe that the volume of injected cement is important to outcome and this volume will be measured. We also hypothesize that fractures in different parts of the spine are subject to different biomechanical forces which affect fracture behaviour. These segments may therefore respond differently to vertebroplasty. We will analyze the sub-groups of thoracic (T4-T10), thoraco-lumbar (T11-L2) and lumbar (L3-L5) as categorized in previous RCTs of spinal augmentation [3,4]. It is our anecdotal belief that the thoraco-lumbar segment is the region of the spine that responds best to vertebroplasty in the acute setting. This is the segment that is exposed to the largest flexion forces and accounts for the majority of “osteonecrotic” fracture clefts filled with either fluid or gas [12-14]. It has been previously demonstrated that thoracolumbar fractures are predisposed to “dynamic mobility” [15] which means that the vertebral body assumes different volumes in the erect and supine (or prone) positions. Such a fracture should benefit the most symptomatic relief from internal fracture fixation afforded by vertebroplasty by reducing fracture fragment motion.

The thoracic vertebrae (T4 to T10) undergo relatively reduced flexion force due to the bracing of the posterior elements by the rib cage. The reduced force across the fracture line in the thoracic segment may imply that natural healing is improved and that less mechanical advantage is obtained from vertebroplasty.

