### Random allocation

The subjects will be randomized to either the control intervention group or the vertebroplasty group using the method of minimization. This will be performed centrally at the National Health and Medical Research Council (NHMRC) Clinical Trials Centre, University of Sydney. The call to the NHMRC Clinical Trials Centre will be made once the patient is in the procedure room immediately prior to the procedure.

Randomization will be 1:1 to each treatment arm, and patients will be stratified by the following factors: * Age (<75, ≥75 years) * Degree of bone height loss (<50%, ≥50%) * Fracture due to trauma (Yes, No) * Patient taking steroids (Yes, No) * Hospital/site.

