### Sample size

The primary outcome is the proportion of patients achieving a 14 day pain score of less than 4 out of 10 (from a baseline score greater than or equal to 7 out of 10). A sample size of 60 patients per arm will have >80% power and 95% confidence to detect a difference in this primary outcome from 35% in the control arm to 65% in the active arm, allowing for a modest loss to follow-up. Recruitment is expected to start November 2011 and take approximately 3 years.

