### Analysis

Effectiveness analyses will be by the intention-to-treat principle, whereby patients are analysed according to the study arm to which they were randomized regardless of the treatment actually received, and toxicity analyses will be according to treatment received. Proportions will be compared using a two-sided chi-squared or exact (conditional binomial) test. Changes in quality of life measures (pain and functional disability scores) will be analysed using *t*-tests to enable comparisons with published studies, and non-parametric tests or regression modelling techniques depending on the distribution of the data. All comparisons will be two-sided with a significance level of 5% considered as being statistically significant. Measures of effect will be presented as either risk differences, odds ratios or mean differences together with the respective 95% confidence intervals.

The primary end point is the proportion of patients whose NRS pain score reduces from 7/10 (or more) to 4/10 (or less) at 14 days. The study sample size is sufficient to detect an absolute difference of 30% in favour of the vertebroplasty arm. Sub-group analysis will also be performed on three different regions of the spine: thoracic (T4 to T10), thoraco-lumbar (T11 to L2) and lumbar (L3-L5). Those patients with two acute fractures involving more than one of these regions will be excluded from this sub-group analysis. We hypothesize that the vertebroplasty efficacy will be maximal in the thoracolumbar group. We expect the benefit will be greater in thoraco-lumbar fractures than in thoracic and lumbar fractures. We hypothesize that the primary end point (pain score <4/10 at 2 weeks) will be achieved in more than 30% additional patients (than control) in the thoraco-lumbar fractures and in less than 30% additional patients (than control) in the thoracic group and the lumbar group. Note that the trial is not specifically powered for this sub-group analysis, and the statistical conclusions that can be drawn from the sub-group analysis will be limited by the number of patients in each sub-group.

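### The spinal-region hypothesis is put in numbers as each region against a fixed 30 points, which does not measure the difference between regions

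*Protocol article*

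**What the plan says.** The section on the mechanics of vertebroplasty gives the rationale for a sub-group analysis by thoracic, thoraco-lumbar and lumbar region, and states the authors' prior: "It is our anecdotal belief that the thoraco-lumbar segment is the region of the spine that responds best" to the procedure. The Analysis section repeats this as a comparative hypothesis, "We hypothesize that the vertebroplasty efficacy will be maximal in the thoracolumbar group", and adds that the benefit there should exceed that in the other two regions.

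The same section then gives the hypothesis in figures. The primary end point "will be achieved in more than 30% additional patients (than control) in the thoraco-lumbar fractures and in less than 30% additional patients" in the thoracic and lumbar groups. The 30 comes from the design of the whole trial: the Sample size section plans "to detect a difference in this primary outcome from 35% in the control arm to 65% in the active arm", and the Analysis section repeats that difference as an absolute 30%.

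The Analysis section also says that the trial was not powered for this sub-group analysis and that its conclusions will be limited by sub-group size. Patients with two fractures in different regions are left out of it. The article names no test for the regional hypothesis.

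**The concern.** The question asked is whether the effect differs between regions. The figures answer another question: on which side of 30 points each region falls. The two can disagree in both directions. True effects of 31 points in thoraco-lumbar and 29 elsewhere fit the numerical hypothesis, although region hardly matters. True effects of 28 points in thoraco-lumbar and 0 elsewhere contradict it, although region matters greatly.

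The choice of 30 makes this worse. If the trial performs as designed and region is irrelevant, every region's true effect lies on the cut-off, and each estimate falls above or below it largely by chance. A reader who holds the published results against the published hypothesis could take such a split as confirmation of a mechanism the authors already believe in.

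**Working it through.** **Inputs from the protocol article.** 60 per arm ("A sample size of 60 patients per arm will have >80% power and 95% confidence"), allocation ("Randomization will be 1:1 to each treatment arm"), 35% versus 65% responders, and two-sided 5% testing ("All comparisons will be two-sided with a significance level of 5% considered as being statistically significant"). Loss to follow-up is given no figure ("allowing for a modest loss to follow-up").

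**Assumptions.** The article does not give the share of patients per region. I take a thoraco-lumbar share of one third to 70%, equal arms within each region, a 35% control rate in every region, and no losses or exclusions. Losses and the exclusion of patients with fractures in two regions would make the regional estimates noisier.

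**Step 1: the plan's own figure.** Power for 35% versus 65% with 60 per arm:

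z = [0.30 − 1.96 × √(2 × 0.5 × 0.5 / 60)] / √[(0.35 × 0.65 + 0.65 × 0.35) / 60] = (0.30 − 0.1789) / 0.0871 = 1.39, so power is 91.8%.

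The stated figure of more than 80% is confirmed. 80% power needs 43 per arm, or 49 with continuity correction.

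**Step 2: precision within a region.** The 95% half-width for a risk difference is 1.96 × √(0.455 / n), with n per arm. It is 34 points for n = 15 and 24 points for n = 30. Estimates this wide cannot be placed reliably on one side of 30.

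**Step 3: how often the hypothesised pattern appears by chance.** The regions are independent, so

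P(pattern) = P(thoraco-lumbar > 30) × P(thoracic < 30) × P(lumbar < 30),

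with each factor from the exact binomial distributions. For 15, 30 and 15 per arm (thoracic, thoraco-lumbar, lumbar) and a common 30-point effect: 0.452 × 0.492 × 0.492 = 0.109.

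The last column is the simulated rate at which a two-sided 5% Wald interaction test (thoraco-lumbar versus the other two pooled, risk-difference scale) rejects in favour of thoraco-lumbar when the common effect is 30 points.

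| Per arm: thoracic / thoraco-lumbar / lumbar | No effect | Common 20 | Common 30 | Common 40 | Interaction test, common 30 |
|---|---|---|---|---|---|
| 20 / 20 / 20 | 1.4% | 9.8% | 8.1% | 2.6% | 3.4% |
| 24 / 24 / 12 | 1.0% | 11.3% | 11.8% | 5.1% | 3.1% |
| 15 / 30 / 15 | 0.4% | 8.9% | 10.9% | 5.5% | 2.8% |
| 18 / 30 / 12 | 0.4% | 8.8% | 10.9% | 5.5% | 2.8% |
| 15 / 36 / 9 | 0.4% | 9.5% | 11.9% | 6.3% | 2.7% |
| 9 / 42 / 9 | 0.2% | 7.0% | 10.4% | 6.5% | 2.5% |

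Under a common 30-point effect the pattern is thus 2.4 (8.1 / 3.4) to 4.4 (11.9 / 2.7) times as frequent as a directional interaction rejection. When the pattern does arise by chance there, the interaction test is significant in only about 18% to 23% of those trials.

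**Step 4: what the interaction test can do.** With 30 per arm in thoraco-lumbar and 30 in the rest, and true effects of 40 versus 15 points, the standard error of the difference is √[(0.2275 + 0.1875) / 30 + (0.2275 + 0.25) / 30] = 0.1725. Power is Φ(0.25 / 0.1725 − 1.96) = Φ(−0.51), about 31%. Over the range of splits, simulation gives 27% to 32% for 40 versus 15 points and 36% to 43% for 40 versus 10.

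**The case against.** The strongest reply is that the article states a hypothesis and no more. Nowhere does it say that a regional claim will be accepted when the estimates fall on either side of 30. As a statement about true effects, more than 30 in one region and less in the others does imply the comparative ordering stated just before it. The authors also limit the conclusions openly. All of this stands, and it rules out several stronger readings that a reader might infer:

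- **That the plan compares regions only with 30 and never with each other.** It does state the between-region expectation in words. Only the numerical version departs from it.
- **That the plan has rejected an interaction test.** The article is silent on the test. The choice may lie in an analysis plan that is not shown, and its absence here is not an error.
- **That the benchmark gives a high chance rate at any sample size.** In simulations with 600 per arm, the pattern appears in 0.2% to 1.0% of trials under a common 20-point effect and in 0.03% to 0.15% under a common 40. With 6,000 per arm both rates are zero. The rate stays near 11% to 12% only when the common effect is 30. For other common effects it is a small-sample problem, which the article's caveat partly covers.
- **That a false regional finding is likely in 20% to 35% of trials.** Figures of that size arise if the other two regions are pooled, or if the result is read as significant in thoraco-lumbar only. The protocol states neither reading.

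What the reply does not remove is that the published number measures something other than the published question. A caveat about power does not change what is being measured.

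**Conclusion.** The point holds as a mismatch between a between-region hypothesis and a numerical benchmark that does not measure the between-region difference. If point estimates are judged against 30, the pattern appears without any regional difference in about 8% to 12% of trials under a common 30-point effect, 7% to 11% under 20, 3% to 6.5% under 40, and at most about 1.4% with no effect. The interaction test's error in the same direction is about 3%. The risk is therefore a false regional claim when a common benefit exists. A claim of benefit where there is none is not the issue.

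These rates rest on the assumed region shares, complete follow-up and equal control rates across regions. The issue is minor: it concerns one caveated secondary analysis and leaves the primary result untouched.

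**What to change.** Replace the 30% benchmark with the estimated difference in treatment effect between thoraco-lumbar fractures and the other two regions together (treatment-by-region interaction, 1 degree of freedom), reported with its 95% confidence interval. Show the risk difference in each region with its confidence interval, as description only. State that any region-specific claim rests on the between-region contrast and is exploratory.

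The cost is a change of wording and one model term on data already collected. The drawback is that the contrast will seldom be conclusive, given power of about 27% to 43% even for 40 versus 15 or 10 points. The confidence interval should therefore carry the message, and a non-significant interaction should not be read as evidence that the regions respond alike.

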### Adverse events

Adverse events will be recorded during the 6 months post procedure. An adverse event is defined as any undesirable experience associated with the use of a medical product in a patient. The event is serious and should be reported within 24 hours when the patient outcome is: death, life-threatening, disability or permanent damage, or the event may jeopardize the patient and may require medical or surgical intervention (treatment) to prevent one of the other outcomes.

An independent safety committee comprising two physicians will review adverse events during the trial. As each serious adverse event (SAE) is reported, one of these physicians will review the details of the SAE within 24 hours. This physician will determine causation (was the SAE deemed related to the procedure or not) and, if related to the procedure, was the event within the adverse events provided in the information and consent.

The safety review committee will review all SAEs every 6 months to determine if each SAE was deemed to have been caused by the procedure or whether the SAE occurred (or could have occurred) as a result of comorbidities and factors other than the procedure.

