Analgesic consumption will be recorded at each time point. This will include the daily dose of each analgesic. Each medication will be classified as “strong opioid”, “mild opioid” or “non-narcotic analgesic” according to opioid comparative information published in the Australian Medicines Handbook [20]. The opioids classified as “strong” include oxycodone, morphine, fentanyl, pethidine, hydromorphone, buprenorphine and tramadol. The opioids classified as “mild” include medications containing codeine or dextropropoxyphene. The non-opioid medications include paracetamol and non-steroidal anti-inflammatory drugs (NSAIDs). The patient will be given a score of 0, 1 or 2 in each of these three analgesic medication categories depending on the number of concurrent different medications being taken within each category. If the patient is taking two different “strong” opioid preparations, for example one prolonged release and another for breakthrough pain, then the score in the strong narcotic category will be 2. If the patient is using one strong opioid medication the score in this category will be 1. If the patient is taking no “mild” narcotics the score in that category is zero. If the patient is taking either paracetamol or an NSAID, then the score in that category will be 1 and if taking both it will be 2. The scores obtained in each of these three categories will be compared between the control and vertebroplasty groups. It is our hypothesis that the “strong opioid” scores in the vertebroplasty group will be lower than those of the control group.

In addition the daily opiate dose will be converted into a morphine dose equivalent using the Opioid Dose Equivalence, Calculation of oral Morphine Equivalent Daily Dose oMEDD) [21], published by the Faculty of Pain Medicine which is a faculty of the Australian and New Zealand College of Anaesthetists. The morphine equivalent daily dose at each data point will be compared between placebo and vertebroplasty groups.

Questions regarding perceived pain change after procedure, blinding and perception of treatment assignment will be administered at 3 days and 2 weeks. A timed get up and go test [22], which is a measure of function in older people, will be performed during clinic visits at baseline, 2 weeks and 6 months. Questions regarding duration of hospitalization, resource use and health care utilization will be collected at 6 months.

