## Discussion

Although the majority of osteoporotic fractures cause minimal morbidity, there is a sub-group of patients that experience severe pain or immobility. This can be a turning point in the life of an elderly patient and can be the difference between independence and institutionalized care. This patient group may develop complications from conservative therapy. Such complications could include narcotic-induced delirium, narcotic-induced constipation, loss of confidence in mobilizing after prolonged bed rest and swelling in the lower legs due to prolonged sitting with the legs not elevated. The principle of acute intervention is to break this downward spiral and allow early mobilization, earlier rehabilitation and recovery of independence.

There are several difficulties in conducting a randomized controlled procedural trial in an elderly population with acute pain. The primary end point of this trial is the numeric rated pain score at 2 weeks. Patient-rated pain score is subjective and can be affected by other factors, particularly the use of narcotic analgesics. For this reason, the trial includes two office visits (at 2 weeks and 6 months, respectively). These visits allow for the collection of a properly performed visual analogue pain score to supplement and compare with the numeric pain score. The office visits do make the trial more difficult to conduct as elderly patients with osteoporotic fractures often have difficulty arranging transportation and require family members, often at their inconvenience, to accompany them.

The Roland Morris Disability score will provide important data as it comprises 24 yes/no questions relating to low back pain and disability. This measure is regarded by the authors as of equal importance to the pain measures. The disability caused by painful spinal fractures is of just as much clinical importance as the pain itself and the 24 yes/no questions are perhaps less subjective than the simple nomination of a pain score. Analgesic use and duration of hospitalization will also provide objective although indirect measures related to pain and disability.

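### The seriousness criteria omit hospital admission and prolonged stay, so an admission that meets no other criterion has no stated route to 24-hour reporting or scheduled serious-event review

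*Protocol article*

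**What the plan says.** The Adverse events section of the protocol article sets out the rule. Its consequence comes first: "The event is serious and should be reported within 24 hours". The trigger is then listed: "when the patient outcome is: death, life-threatening, disability or permanent damage, or the event may jeopardize the patient". The last part of that list carries a further condition, namely that the event "may require medical or surgical intervention (treatment) to prevent one of the other outcomes". This gives three named outcomes (death, threat to life, and disability or lasting damage) and one clause that rests on judgement, called the jeopardy clause below.

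The same section describes the review:
- In general: "An independent safety committee comprising two physicians will review adverse events during the trial".
- For each serious event as it is reported: "one of these physicians will review the details of the SAE within 24 hours", with a decision on causation and on whether the event was covered by the consent information.
- Periodically: "The safety review committee will review all SAEs every 6 months", again to judge causation.

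Hospitalization appears elsewhere. The Measures section states: "Questions regarding duration of hospitalization, resource use and health care utilization will be collected at 6 months". Table 2 agrees, marking resource use at the 6-month visit only. The Discussion explains its purpose: "Analgesic use and duration of hospitalization will also provide objective although indirect measures related to pain and disability". Table 2 also marks adverse events at all five follow-up contacts (day 3, day 14 and months 1, 3 and 6).

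**The concern.** Admission to hospital, or a longer stay because of a new event, is an observable fact that needs little interpretation. The article leaves it out of the criteria, so the seriousness of an admission that ends in recovery depends on how someone at one of the four centres reads the jeopardy clause.

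This matters in the population described. The Discussion names opioid-induced delirium, the effects of prolonged bed rest and loss of independence as the morbidity to expect. The Measures section foresees patients still in hospital at day 3, so a prolonged stay is possible as well as a readmission.

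Two things are at stake: prompt review of individual events, and a serious-event count that means the same thing at each centre when the arms are compared. The primary end point and its analysis are not at stake.

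**Working it through.** No figure in the article bears on this point, so the check is a reading of the passages side by side.

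**Step 1: does an admission meet the rule as written?** Take a hypothetical patient who goes home, is readmitted in week 3 with a chest infection or delirium, and recovers.

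| Criterion in the Adverse events section | Met by this admission? |
|---|---|
| Death | No |
| Threat to life | Only if the illness was that severe |
| Disability or lasting damage | Not if recovery is full |
| Jeopardy clause | Only if someone judges that the patient was in jeopardy and that treatment might be needed to avert one of the outcomes above |

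The jeopardy clause refers back to the named outcomes. Being admitted does not satisfy it; a judgement about what might otherwise have happened is needed. Some admissions will pass that test and others will not.

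**Step 2: what depends on the answer?**

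| Review step | Applies to |
|---|---|
| Report within 24 hours | Serious events |
| Physician review within 24 hours, with causation | Serious events |
| Committee review every 6 months | Serious events |
| Committee review during the trial, with no interval or procedure stated | Adverse events in general |

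The first three rows have a timetable and all require seriousness. The fourth is not limited to serious events, but nothing says when or how non-serious events reach the committee.

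**Step 3: by what other route could the admission be seen?**
- *Adverse-event record.* The infection or delirium can be recorded at the next contact, month 1 for the patient above. Table 2 does not show whether admission is noted with it. The article defines an adverse event as an undesirable experience associated with use of a medical product. A site could read that as excluding an illness it attributes to comorbidity.
- *Hospitalization questions.* These come once, at 6 months, under resource use. A patient who has died or been lost by then does not answer them. Death is itself a listed criterion, but an earlier non-fatal admission in that patient would not be picked up by these questions.

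**Step 4: how large is it?** The article gives no rate of admission, readmission or prolonged stay, so the number of events outside the three timed reviews cannot be calculated. On timing, the planned size is 2 × 60 = 120 patients and 112 were enrolled by 5 September 2014, leaving 120 − 112 = 8 to enrol. A change would therefore act mainly on remaining follow-up and on the final safety tables.

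**The case against.** The strongest reply is that the article leaves several routes open. The general sentence on the committee covers adverse events without restriction, and adverse events are sought at five contacts. The jeopardy clause is broad: a frail patient readmitted for treatment of delirium or infection, or disabled by a new fracture, could well be classed as serious. All of this stands, and it limits the point.

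A reader might infer that many readmissions never reach the committee, that the serious-event count is understated, or that a cluster of admissions could not be noticed. The documents do not support these readings. There is no admission rate behind *many*. The general review sentence and the five contacts rule out *never*. Nothing shows how sites apply the jeopardy clause, so understatement and variation between sites are possibilities, not facts. The 6-monthly review is given the task of judging causation; the article describes no monitoring for clusters that the omission would defeat.

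It can also be said that the article does not contradict itself. Duration of hospitalization is used as an indirect measure of pain and disability, not as a safety trigger, and that is correct. The point is a weakness in a rule, not an inconsistency.

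Finally, an article condenses a fuller protocol, which may define seriousness more widely. That would be an answer if the article were silent. It prints an operative rule with its criteria, so the rule can be judged as printed.

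**Conclusion.** The point holds in a limited form. As printed, the criteria omit hospital admission and prolonged stay. An admission that meets no named outcome, and is not judged to come under the jeopardy clause, has no stated route to 24-hour reporting, 24-hour physician review or the 6-monthly serious-event review. The event behind it may still be recorded and may still be seen by the committee, but on no stated timetable.

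The size is unknown and no count should be attached to it. The conclusion rests on reading the printed criteria as the rule that sites follow. It is a cheap improvement to safety capture and to the comparability of serious-event counts across the four centres; it does not bear on the efficacy result.

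**What to change.** - **Criteria.** In the Adverse events section, add to the reporting criteria: unplanned admission to hospital, or prolongation of an existing admission due to a new event. State that the index stay of a patient enrolled as an inpatient does not count.
- **Collection.** Ask about admissions at the existing adverse-event contacts (day 3, day 14 and months 1, 3 and 6), and keep the 6-month resource-use questions as they are.
- **Events already recorded.** Reclassify them against the amended criteria, so that one definition applies to the whole trial.
- **Reporting.** Present serious events by arm, with those serious through admission shown separately, so that counts on the present criteria can still be read off.

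The cost is one criterion, one item on the adverse-event form and a pass through the existing records. The two safety physicians will receive more reports, many of them for comorbid illness. With 112 patients already enrolled, the gain lies mainly in the remaining follow-up and the final safety report.

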**Table 2 Tab2:** **Schedule for data collection**

**Evaluations**	**Visit baseline**	**Phone day 3**	**Visit day 14**	**Phone 1 month**	**Phone 3 month**	**Visit 6 month**
Procedure/operative information	X					
Pain NRS Questionnaire	X	X	X	X	X	X
Pain VAS Questionnaire	X		X			X
Physicians VAS Questionnaire	X		X			X
Roland-Morris Low Back Pain and Disability Questionnaire	X	X	X	X	X	X
Osteoporosis Quality of Life Questionnaire (QUALEFFO)	X		X	X		X
EQ-5D Questionnaire	X	X	X	X	X	X
Change in pain		X	X			
Perception of treatment assignment		X	X			
Pain medication	X	X	X	X	X	X
Timed up and go test	X		X			X
Adverse events		X	X	X	X	X
Resource use/health care utilization information						X
Erect spinal X-ray	X					X

The numeric rated scale (NRS) of pain will be used at all data collection points. Patients will be asked to answer with a number between 0 to 10 to estimate their pain intensity. This is the primary outcome measure. To standardize results, the primary pain question is the same as that used in the INVEST Trial [16], the larger of the published blinded trials of vertebroplasty. This primary pain score will record pain over the previous 24 hours. Separate numeric pain scores at rest and during standing or moving will also be obtained.

Visual analogue scale (VAS) of pain will be recorded at the three clinic visits (baseline, 2 weeks and 6 months post procedure). This score will be obtained by asking the patient to make a mark on a line which is 10 cm in length in answer to the primary pain question. The line is marked “no pain” at the left extreme and “worst possible pain” at the right extreme. There are no other divisions or marks on the line. This VAS measure is recorded for overall pain over previous 24 hours as well as separate measures for pain at rest and during walking or activity. This VAS pain score will supplement the NRS pain score at these three time points including the primary end point (NRS pain at 2 weeks post procedure). The subjective nature of patient reported pain is problematic and thus the dual pain measurements. The researcher will also record their own estimate of patient pain at the clinic visits.

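### The causality rule for serious adverse events leans towards the procedure not being the cause, and the event definition, recording window and list of serious outcomes leave gaps

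*Protocol article*

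**What the plan says.** All of the rules stand in the Adverse events section of the protocol article, except the schedule (Table 2) and the analysis set (Analysis).

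- Definition: "An adverse event is defined as any undesirable experience associated with the use of a medical product in a patient".
- Window: "Adverse events will be recorded during the 6 months post procedure". In Table 2 the row reads "Adverse events X X X X X". The five marks are at day 3, day 14 and months 1, 3 and 6. The baseline column, which holds the procedure/operative information, has no adverse event mark.
- Seriousness: an event is serious when "the patient outcome is: death, life-threatening, disability or permanent damage", or when it may endanger the patient and may need treatment to avert one of those outcomes. Hospital admission and prolonged stay are not named.
- First causality review, by one physician within 24 hours: "This physician will determine causation (was the SAE deemed related to the procedure or not").
- Second causality review: "The safety review committee will review all SAEs every 6 months", to decide whether each was caused by the procedure or "whether the SAE occurred (or could have occurred) as a result of comorbidities and factors other than the procedure".
- Analysis: "toxicity analyses will be according to treatment received", with no restriction to related events.

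**The concern.** A causality classification is useful only if each event fits one class and doubt is handled evenly. Here doubt has one destination. Almost any chest event, new fracture or death in this population could have arisen without the procedure, so a committee that follows the wording would seldom attribute an event to it. At stake is the number of procedure-related SAEs, which clinicians and patients will look for when they weigh an invasive treatment.

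The other three wordings act earlier, at capture. A condition of association in the definition, a window that does not expressly include the procedure, and a seriousness list without admission can each keep an event from being recorded as an adverse event or from reaching 24-hour review.

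**Working it through.** The article states no adverse event rate and no power for safety, so there is no safety figure of the plan to reproduce. Its sample size of 60 per arm serves the primary outcome and is used below only as a denominator. Most of the check consists of setting statements side by side.

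1. **Overlap of the committee's classes.** Let C mean that the procedure caused the event, and O that another cause is possible. The first class needs C; the second is met by O. An event with both C and O meets both, and no tie rule is given. There is no mirror class for events that the procedure may have caused. Applied literally, only events with C and without O are safe in the first class.

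2. **Two tests for one event.** The first physician asks only whether the event is related. The committee adds the possibility clause. The same SAE can be related at 24 hours and not attributed at the six-monthly review, and the article does not say which answer stands.

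3. **Size of the downward bias (assumed inputs).** Let T be the number of SAEs truly caused by the procedure and q the share of them that also has another possible cause. The number that stays attributed is T × (1 − q). With T = 6 among 60 patients (6/60 = 10%):

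| q | Attributed | Per 60 |
|---|---|---|
| 25% | 6 × 0.75 = 4.5 | 7.5% |
| 50% | 6 × 0.50 = 3.0 | 5.0% |
| 75% | 6 × 0.25 = 1.5 | 2.5% |
| 90% | 6 × 0.10 = 0.6 | 1.0% |

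 With T = 3 the attributed counts are 2.25, 1.5, 0.75 and 0.3. The proportion lost is q, whatever T is.

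4. **Effect on all SAEs by arm.** The rule moves an event between classes within its arm, so the arm total is unchanged. That comparison is, however, imprecise. With 60 per arm, a two-sided 5% level and the normal approximation, power = Φ{[d√n − 1.96√(2p̄(1 − p̄))] / √[p₁(1 − p₁) + p₂(1 − p₂)]}, where d = p₂ − p₁ and p̄ is their mean. Assume that 10% of controls have an SAE. For an excess of 10 points this is Φ{(0.775 − 0.990)/0.5} = 33%. For excesses of 5 and 15 points it is 13% and 58%. Readers may therefore lean on the attributed count.

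5. **Definition against review.** The definition asks for association with a product before an experience counts as an adverse event. The committee is later asked to find SAEs due to comorbidity. If the first condition is applied strictly, some of the events that the second step is meant to find need not have been recorded.

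6. **Window against Procedures.** Procedures foresees venous, disc or spinal canal extrusion of cement during injection, and both arms receive intravenous midazolam and fentanyl. The wording of the window and Table 2 start adverse event recording afterwards.

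7. **Seriousness.** An admission is serious only if it also meets the clause on endangering the patient. Other admissions would appear only as ordinary adverse events, or in the hospitalization and resource-use questions at 6 months.

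**The case against.** The strongest reply is that this is a matter of wording with no shown effect on the main comparison of harm. Much of that is fair.

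A reader might infer that SAEs with another possible cause are set aside. The documents do not say so: the committee reviews all SAEs, the disputed sentence only assigns cause, and the toxicity analysis is not limited to related events.

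A reader might also infer that events are collected unequally by arm, since a sham patient receives no cement. The documents do not support this either. There is one schedule for both arms, patients and data collectors are blinded, controls also receive sedation and local anesthetic, and X-rays look for incident fractures in both groups. Unequal capture would follow only if the product in the definition were read as the cement or its kit.

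On the window, operative information and cement volume are recorded and oximetry is continuous, so procedural events need not be lost; the full form may name them. On admissions, the clause on endangering the patient covers some, and the committee also reviews adverse events in general. How safety tables are laid out may be settled in an analysis plan that is not shown.

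These replies narrow the point but do not remove it. The overlap, the one-sided test, the mismatch between the two reviews and the condition of association are stated in the article; they are not gaps left by condensation. The reply that all SAEs are counted also depends on the definition having let them in.

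**Conclusion.** The safety rules are badly fixed and should be corrected. The committee's rule, if followed literally, biases the count of procedure-related SAEs downwards by the share of such events that has another possible cause. The documents give no value for that share; the 25% to 90% range is an assumption, chosen because an alternative cause will often be conceivable in osteoporotic patients over 60. A committee that used ordinary judgement despite the wording would show less bias.

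The count of all SAEs by arm is unaffected by this rule. The definition, the window and the seriousness list could lead to under-capture of events or under-reporting of them as serious, by an amount that cannot be estimated from the article. Neither exclusion of events from analysis nor unequal collection between arms is part of the conclusion. The primary outcome is not touched.

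**What to change.** - Define an adverse event as any untoward event in either arm, from the start of sedation to 6 months, whatever its cause and without a link to a product. Add an adverse event mark for the procedure in Table 2.
- Add hospital admission or prolonged stay to the serious outcomes.
- Delete the bracketed possibility clause from the committee's rule. Use one scale with exclusive classes (related, possibly related, unrelated) for both reviews, and state whose answer stands.
- Report all SAEs by treatment received irrespective of attribution, with attribution as a secondary table.

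The cost is wording, a form change and more events to report. Randomization and the primary endpoint are unchanged. Trial status gives 112 patients enrolled of 2 × 60 = 120, so most of the work is retrospective. SAEs already reported can be reclassified on the new scale. Whether unrecorded procedural events and admissions can be recovered depends on procedure and hospital records that the article does not describe, and any remaining gap should be stated in the report.
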